**Additional inclusion criteria, high risk arm (at least 1 factor to be fulfilled):**
• R1 resection and/or
• pT4 status and/or
• > 3 lymph node metastases and/or
• Extracapsular spread of lymph node metastasis
**Additional inclusion criteria for intermediate risk arm (at least 1 factor to be fulfilled):**
• pT3R0 and/or
• 1-3 lymph node metastases and no extracapsular spread of lymph node metastasis
Exclusion criteria:
• Cumulative nicotine abuse > 30 packyears for intervention arms. These patients are always included in control arms (regardless of HPV status).
• M1
• R2 resection
• No neck dissection performed
• >7 weeks interval surgery-radiotherapy
• Contraindication for guideline-compliant adjuvant radio(chemo)therapy according to clinical risk constellation
• Malignant tumour disease in the last five years before start of study (except basal cell carcinoma of the skin, in-situ carcinoma of the cervix uteri or breast or tumours with a similar good prognosis that are considered very likely to be cured)
• Any malignant tumour disease in the head and neck region regardless of interval and prognosis
• Previous radiotherapy with potential overlap
• Participation in another clinical trial if, and as result of this, another experimental therapy is necessary or the therapies/study protocols are mutually exclusive (e.g. modified chemotherapy, additional consolidating chemotherapy; immunotherapy). Additional participation in observational studies or supportive therapy studies are allowed
• Any other diseases or conditions that do not allow the patient to assess the nature and scope as well as possible consequences of the clinical study
• Pregnant or breastfeeding women

Dose de-escalation is performed in two steps with a dose-reduction by 10% each. The second dose de-escalation step is opened, when all of the planned 30 patients were accrued to the respective interventional arm, when at least 10 out of 30 patients finished their 24 months follow-up time and if the first stopping criterium (two recurrences within 24 months follow-up among the first 10 patients in the respective interventional arm) has not been reached. Patients enrolled after closure of the de-escalation arms, are being included in the observational arm and receive standard radio(chemo)therapy.

The flowchart of the study is depicted in Fig. 1. Patients with operable OPSCC and indication for adjuvant radio(chemo)therapy, as recommended by the experts in the interdisciplinary tumour board for malignancies of the head and neck, are offered to participate in this clinical trial. After patient’s consent and consultation, FFPE tumour material is analysed centrally at the Institute of Pathology at the University Hospital Dresden and includes HPV analysis using p16 immunohistochemistry and PCR-array based HPV DNA genotyping. Patients with proven HPV-association of their tumours, e.g. positivity for both p16 (defined as continuous, strong block-type p16-positivity of the cytoplasm and/or nuclei in at least 70% of the tumour cells [24]) and HPV16 DNA (polymerase chain reaction (PCR)-array based analysis), are subjected to the interventional arm according to their risk for recurrences [intermediate-risk (IR) vs. high-risk (HR)] and treated with 10% dose reduction to both the former tumour bed and the lymph node levels. Patients without HPV-associated tumours are being allocated to the observational arm and are receiving standard radio(chemo)therapy within this prospective trial. After enrollment of 30 patients per risk-arm, patients are also being enrolled in the observational arm A or B (according to their risk profile) until a minimum follow-up of 2 years has been reached for 10 patients for the respective arm. For these patients, HPV is assessed but standard radio(chemo)therapy is applied irrespective of its result. The cohorts of the observational arms are serving as comparison group.

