Proton therapy may also be an option to achieve high response rates with lower doses to organs at risk and therefore a potential reduction in late toxicities. Even though proton therapy is currently not widely available, it is allowed within the DELPHI trial presented here in order to open the possibility for comparison between both treatment modalities.

As mentioned above, smoking is one of the risk factors for the development of HNSCC. According to Ang et al. [24], cumulative nicotine abuse of more than 10 years may be associated with lower local control rates. However, this could not be confirmed by epidemiological studies or clinical data sets [25–27]. Within the current study, patients with a cumulative nicotine abuse of at least 30 packyears are being excluded from dose de-escalation and are enrolled in the observational arm.

Overall, patients with HPV-positive OPSCC are characterised by higher local control rates in comparison to those with HPV-negative disease. The hypothesis of our study is that moderate dose reduction does not lead to an increase of locoregional recurrences but results in less late side effects. Within this study, the HPV status is analysed centrally and includes p16 immunohistochemistry and HPV DNA genotyping. HPV-positive tumours are characterised by p16 overexpression of at least 70% of the tumour cells and HPV16 DNA positivity to ensure as much as possible that patients with truly HPV-driven tumour are being enrolled in the interventional arms [28].

Nevertheless, the potential risk of increased recurrences cannot be fully ruled out and is being monitored by several instances, including dummy runs of a treatment plan, quality control and central review of the first three treatment plans per center, central HPV analysis, stopping criteria of the study and step-wise reduction of the total dose including a monitoring time of 24 months of patients with intermediate- as well as in patients with high-risk disease.

The study protocol has been prepared in accordance with the SPIRIT (Standardised Protocol Items: Recommendation for Interventional Trials) guidelines [29].

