### Statistics

We calculated stopping criteria, i.e. the number of recurrences, for which the trial has to be stopped, considering (interim) analyses after 10, 20 and 30 patients have completed 2-year follow-up. Assumptions are: expected recurrence rate: 0.03 in the de-escalation arms, maximum tolerated recurrence rate: 0.1, probability of stopping the study in error despite the expected recurrence rate is achieved: α < 0.1, probability of correctly stopping the study if the recurrence rate is too high: 1-β > 0.6. The calculated numbers that lead to the study being stopped are: 2 recurrences among the first 10 patients, 3 recurrences among the first 20 patients, 3 recurrences among the first 30 patients. The calculation was performed using the toxbdry function of the clinfun package in R statistics software, which applies a Pocock-type boundary for repeated testing [36–38].

For each of the two interventional arms, 60 patients per risk-profile are necessary (*n* = 120 patients in total), i.e. 30 patients in dose-de-escalation step 1 and 30 patients in dose-de-escalation step 2. After closure of the first dose de-escalation step and before opening of the second dose de-escalation step, patients are being enrolled in the respective observational arm according to their risk profile.

It has been assumed that about 50% of the OPSCC are HPV-driven (defined by p16 overexpression and HPV16 DNA positivity). In addition, it is supposed that 6% of the patients will die before the 24 months follow up has been reached or will withdraw from the study during follow-up. In addition, a dropout rate of 15% is assumed. This leads to 152 patients to be enrolled in the HPV-positive interventional arms. In parallel, about 152 patients will be enrolled in the respective observational arms including drop-outs. The total patient number is thus 304. Additional patients will be enrolled in the observational arm between closure of dose step 1 and opening of dose step 2.

The number of patients in the observational arms is not restricted. The observational arm closes when the interventional arms of the second dose de-escalation step closes.

Missing data will be handled using appropriate statistical methods depending on the type and extent of missingness. Sensitivity analyses may be performed if applicable.

Additional subgroup analyses may be performed for the high-risk and intermediate-risk cohorts.

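### Opening of the second de-escalation step depends on the first look (2 of 10) only, which blocks a 10% recurrence rate with probability 0.26, against 0.61 for the three-look rule

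*Protocol article*

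**What the plan says.** The Study design section, in the paragraph after Table 1, sets three conditions for opening the second step in a risk arm. All 30 step 1 patients must be accrued; the rest reads "when at least 10 out of 30 patients finished their 24 months follow-up time and if the first stopping criterium", defined there as two recurrences within 24 months among the first 10 patients of that arm, has not been reached. The next paragraph of the same section is consistent with this: after the 30th patient, new patients go to the observational arm until 10 patients have two years of follow-up.

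The Statistics section gives a rule with three looks, "considering (interim) analyses after 10, 20 and 30 patients have completed 2-year follow-up". The counts that stop the trial are "2 recurrences among the first 10 patients, 3 recurrences among the first 20 patients, 3 recurrences among the first 30 patients". The design rates are "expected recurrence rate: 0.03 in the de-escalation arms, maximum tolerated recurrence rate: 0.1", and the stated error rates are "probability of stopping the study in error despite the expected recurrence rate is achieved: α < 0.1" and "probability of correctly stopping the study if the recurrence rate is too high: 1-β > 0.6".

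The Introduction lists the stopping criteria and the "step-wise reduction of the total dose including a monitoring time of 24 months" among the safeguards against excess recurrences. Data management and monitoring provides an independent committee that works from the predefined stopping rules. Perspective says that the study group decides how to proceed if stopping criteria are reached.

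**The concern.** The opening of step 2 is the point at which new patients are first exposed to the deeper dose reduction. By then step 1 in that arm is fully accrued, so its looks at 20 and 30 patients can protect new patients only through their effect on step 2. The opening rule uses one look out of three and ignores what is already known about 20 of the 30 step 1 patients. The Statistics section describes protection of more than 0.6 at a 10% rate, but the opening decision carries much less than that. Step 2 patients could be enrolled while step 1 is about to reach one of its own boundaries. If three recurrences are already known in patients 11 to 30, one section permits opening and the other already makes the 3-in-30 boundary certain.

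**Working it through.** **Inputs, all from the article.** Recurrence rates 0.03 and 0.10; looks at 10, 20 and 30 patients; boundaries 2, 3 and 3 (Statistics). The opening condition uses the first boundary only (Study design). A rate of 0.20 is added for illustration. Calculations are per arm and treat the 24-month outcome as binary, independent between patients and completely observed.

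**Step 1: the first look alone.** P(block) = 1 − P(0 of 10) − P(1 of 10).

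- 3%: 1 − 0.7374 − 0.2281 = 0.0345
- 10%: 1 − 0.3487 − 0.3874 = 0.2639
- 20%: 1 − 0.1074 − 0.2684 = 0.6242

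**Step 2: the plan's own figures for the three-look rule.** Counts cannot fall, so an arm escapes all three boundaries only with 0 in the first 10 and at most 2 in the next 20, or with 1 in the first 10 and at most 1 in the next 20. P(escape) = P(0 of 10) × P(≤2 of 20) + P(1 of 10) × P(≤1 of 20).

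- 3%: 0.7374 × 0.9790 + 0.2281 × 0.8802 = 0.923, so P(stop) = 0.077
- 10%: 0.3487 × 0.6769 + 0.3874 × 0.3917 = 0.388, so P(stop) = 0.612
- 20%: 0.1074 × 0.2061 + 0.2684 × 0.0692 = 0.041, so P(stop) = 0.959

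The stated limits (below 0.1 at 3%, above 0.6 at 10%) are reproduced. Split by look, the 10% figure is 0.2639 + 0.1267 + 0.2216 = 0.6122.

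**Step 3: what follows once the gate is passed.** P(later step 1 crossing | gate passed) = (P(stop) − P(block)) / (1 − P(block)). At 10% this is (0.6122 − 0.2639) / 0.7361 = 0.3483 / 0.7361 = 0.47.

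| True rate | Gate as written blocks | Gate passed | Three-look rule stops | Later crossing, given gate passed |
|---|---|---|---|---|
| 3% | 0.035 | 0.966 | 0.077 | 0.04 |
| 10% | 0.264 | 0.736 | 0.612 | 0.47 |
| 20% | 0.624 | 0.376 | 0.959 | 0.89 |

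**Step 4: adding what is already known at opening.** Suppose opening is also blocked by 3 or more recurrences among all 30, each within 24 months of the end of therapy and known on that date. The article does not give the length of step 1 accrual, so this needs assumptions: uniform accrual over 18 to 60 months, constant hazard, 1.25 months of radiotherapy, and opening when 30 are accrued and the tenth patient reaches 24 months. In 200,000 simulated cohorts per setting, blocking at 10% was 0.506, 0.467, 0.399, 0.414 and 0.447 for accrual over 18, 24, 36, 48 and 60 months. At 20% it was about 0.83 to 0.91. At 3% it was about 0.045 to 0.06.

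The 3% figure cannot exceed 0.077 whatever the accrual pattern, because any arm blocked this way would also cross one of the plan's own boundaries. The 24-month limit is needed for this. Counting every recurrence known on the date, however late, blocks a 3% arm with probability of about 0.09 at 60-month accrual.

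**The case against.** A reader might infer that the 20- and 30-patient boundaries protect nobody, and that an unacceptable rate goes undetected with 74% probability. The article does not support this. The Statistics section makes all three counts stopping numbers for the trial, not for step 1 accrual alone. A monitoring committee works from them, and Perspective provides for a decision when one is reached. They can act after step 2 opens. They could also act before it, if 20 patients happen to have completed follow-up by then. The figure of 0.736 is the chance of passing the gate; the chance of escaping the whole rule at 10% is 0.388.

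Nor is any stated error rate wrong. The limits are attributed to stopping the study, never to the opening decision, and they reproduce. The article calls 10% the "maximum tolerated recurrence rate: 0.1", although its power statement treats that rate as too high. Opening after partial follow-up is an open trade-off and one of several listed safeguards. The effect of a late crossing on an open step 2 may be laid down in the full protocol or the committee's charter, which are not shown.

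All of this stands. It does not remove the point that the article states the opening rule explicitly and names one boundary out of three. That rule sits awkwardly with trial-level boundaries that may already be certain to be crossed on the opening date.

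**Conclusion.** The point holds as a weakness in the opening rule and a gap between two sections, not as an error in the stated α or power. The decision to start the deeper reduction has a 0.26 chance of being blocked at a true 10% rate and 0.62 at 20%, against 0.61 and 0.96 for the full rule. Part of that difference is the price of not waiting for all 30 patients to complete follow-up. The rest comes from leaving out recurrences already known. The article also leaves open what a later step 1 crossing means for an open step 2, an event with probability 0.47 at a true 10% once the gate is passed. The binomial figures are exact under independence and complete follow-up. The figures for the amended gate also depend on the assumed accrual and hazard.

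**What to change.** Reconcile the opening rule in Study design with the boundaries in Statistics, using the plan's own numbers.

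- State that, on the opening date, an arm with 3 or more recurrences within 24 months of the end of therapy already known among its 30 step 1 patients counts as having reached its stopping criterion, in addition to the existing 2-in-10 condition. Keep the 24-month limit in the wording.
- State that a later step 1 crossing of 3 in 20 or 3 in 30 applies to step 2 accrual in the same arm, through the monitoring committee.

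The cost is a short amendment to the protocol and the committee's charter, and a recurrence status for all 30 step 1 patients on the opening date. No follow-up is added before opening. The downside is a somewhat higher chance of wrongly holding back step 2 at a 3% rate: about 0.045 to 0.06 under the assumptions above and never more than 0.077, against 0.035 now.

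### Study design fills a de-escalation cohort at 30 enrolled, while Statistics implies about 38; if the cap of 30 is applied as written, the stated 1-β > 0.6 is not met

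*Protocol article*

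**What the plan says.** All references are to the protocol article.

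- **Study design, flowchart paragraph:** "After enrollment of 30 patients per risk-arm, patients are also being enrolled in the observational arm A or B". This lasts until 10 patients of the respective arm have two years of follow-up. These later patients receive standard treatment whatever their HPV result.
- **Study design, paragraph after Table 1:** the second step opens "when all of the planned 30 patients were accrued to the respective interventional arm", provided that at least 10 of those 30 have finished 24 months and the first stopping limit has not been reached.
- **Statistics, stopping rule:** limits were calculated "considering (interim) analyses after 10, 20 and 30 patients have completed 2-year follow-up". They are 2 recurrences in the first 10, 3 in the first 20 and 3 in the first 30. The design assumes a true rate of 3% in the de-escalated patients, takes 10% as the most it will accept, and keeps false stopping (α) below 0.1. Its target for detection is "probability of correctly stopping the study if the recurrence rate is too high: 1-β > 0.6".
- **Statistics, sample size:** 30 patients are necessary per risk profile and dose step, 120 in all. Statistics assumes 6% death or withdrawal before 24 months and a further 15% dropout. "This leads to 152 patients to be enrolled in the HPV-positive interventional arms".

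The article does not mention replacement of lost patients and does not define an accrued patient as one who is evaluable at 24 months.

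**The concern.** The number 30 has two meanings. In Study design it counts patients entered, and it triggers diversion to the observational arms. In Statistics it counts patients with completed follow-up, and more must be enrolled to obtain it. Four cohorts capped at 30 enrol 120 patients, not 152.

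The stopping rule is one of the safeguards that the Introduction names against excess recurrence, and locoregional recurrence is the primary endpoint. The rule clears its own target of 0.6 by only about 0.012, and its third look supplies more than a third of the stopping probability at the 10% rate. A cohort that falls short of 30 with completed follow-up therefore misses a stated design property.

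**Working it through.** **Inputs (all from Statistics).** Recurrence rates 0.03 and 0.10; limits 2/10, 3/20, 3/30; losses 6% and 15%; 120 patients necessary; 152 enrolled.

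**1. The planned enrolment.** 120 / (1 − 0.06 − 0.15) = 120 / 0.79 = 151.9, rounded up to 152. Per cohort, 152 / 4 = 38, and 38 × 0.79 = 30.0 expected with completed follow-up. (Compounding the losses gives 120 / (0.94 × 0.85) = 150.2, so 151; the choice hardly matters.) The 30 in Statistics is therefore a number after losses.

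**2. The stated rule.** Exact binomial recursion: at each look, add the probability of reaching the limit, carry forward only the outcomes below it, and add the next patients as a new binomial count.

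At a rate of 0.10:
- Look at 10, limit 2: P(0) = 0.9^10 = 0.3487 and P(1) = 10 × 0.1 × 0.9^9 = 0.3874. P(stop) = 1 − 0.3487 − 0.3874 = 0.264.
- Look at 20, limit 3: a further 0.127, cumulative 0.391. The continuing outcomes are 0, 1 or 2 recurrences, with probabilities 0.1216, 0.2702 and 0.2176.
- Look at 30, limit 3: a further 0.222, cumulative **0.612**.

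At a rate of 0.03 the cumulative values are 0.035, 0.044 and **0.077**. Both stated limits (α < 0.1, 1-β > 0.6) are met. The third look supplies 0.222 / 0.612 = 36% of the stopping probability at 10%.

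**3. The cap of 30 enrolled, applied as written without replacement.**
- All 21% lost after accrual: 30 × 0.79 = 23.7, about 24 evaluable.
- Only 6% lost after accrual: 30 × 0.94 = 28.2, about 28 evaluable.
- For a final look at 24 (four more patients, limit 3), the stopping probability added after the look at 20 is 0.2176 × (1 − 0.9^4) + 0.2702 × P(≥2 of 4) + 0.1216 × P(≥3 of 4) = 0.2176 × 0.3439 + 0.2702 × 0.0523 + 0.1216 × 0.0037 = 0.089. The total is 0.391 + 0.089 = 0.480.
- A final look at 28 adds 0.179 in the same way, for a total of 0.570.
- If lost patients stay in the denominators and half of their recurrences are seen before loss, the effective rate is 0.10 × (0.79 + 0.21/2) = 0.0895. The 10/20/30 rule then gives 0.537. If none of their recurrences are seen, the rate is 0.079 and the result 0.454.

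| Situation | P(stop at 10%) |
|---|---|
| 38 enrolled, 30 evaluable | 0.612 |
| 30 enrolled, 6% lost, final look at 28 | 0.570 |
| 30 enrolled, 21% lost, half of their recurrences seen | 0.537 |
| 30 enrolled, 21% lost, final look at 24 | 0.480 |
| 30 enrolled, 21% lost, counted as recurrence-free | 0.454 |
| 30 enrolled, third look never held | 0.391 |

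If the number evaluable is treated as random, Binomial(30, 0.79), the values are 0.386 without a final look and 0.473 with one. At a rate of 0.03 the false-stopping probability is 0.044 with looks at 10 and 20 only, and 0.055 with a final look at 24. The cost therefore falls on 1-β, not on α.

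**4. Opening of step 2.** This depends on the first look only. Its stopping probability at the 10% rate, 0.264, is the same whether 30 or 38 are enrolled.

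**The case against.** The strongest reply is that Statistics has already dealt with losses. It plans 152 enrolled, which keeps about 30 evaluable per cohort and 1-β at 0.612. On that view the 30 in Study design is shorthand for the target before inflation. This reading is plausible, and it is why the shortfall can only be stated conditionally. It does not remove the conflict. Study design is the text that says when patients are diverted, it speaks of enrolment and accrual, and its own condition of 10 out of 30 with finished follow-up shows that its 30 includes patients still being followed. No closure rule in the article implements the 152.

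A second reply is that 0.39 to 0.48 is the pessimistic end. The article does not say when the 15% dropout occurs, a recurrence seen before withdrawal is an observed event, and a final analysis may well be held. All of this stands, which is why the range runs up to about 0.57. Every case examined is still below 0.6.

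A reader might go further and infer that the trial's 1-β has in fact dropped to 0.39–0.48, or that step 2 would open on a weakened check. The documents support neither. The first takes one side of a contradiction as the settled design, and the second overlooks that the opening condition uses the first look alone.

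That the source is a condensed article does not answer the point. The objection is to two incompatible enrolment numbers that are both stated, not to missing detail.

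**Conclusion.** The point holds as an internal contradiction with a conditional consequence. The stopping limits, both error probabilities and the 152 are correctly calculated; the conflict is between 30 enrolled in Study design and the 38 per cohort implied by Statistics. If the cap of 30 is followed without replacement, the stopping probability at the maximum tolerated rate falls from 0.612 to between about 0.39 and 0.57. The value depends on how many patients are lost after accrual, whether their earlier recurrences count, and whether a final look is held on fewer than 30. Under the lower values (0.39 to 0.48) a cohort with a true 10% rate is more likely than not to pass; under 0.54 or 0.57 it is not, but the stated target is still missed. If 38 are enrolled and losses are as assumed, nothing is lost.

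**What to change.** Reconcile the two sections. In both paragraphs of Study design, state the accrual cap as about 38 enrolled per risk arm and dose step, expected to give 30 with completed 2-year follow-up, to match the 152 in Statistics. Leave the separate condition of 10 patients with 24 months of follow-up as it is. Do not write the cap as 30 evaluable patients: evaluability is known only at 24 months, so read literally that would hold step 2 until 30 patients had finished follow-up.

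For any cohort already closed at 30 enrolled, hold the final look on the patients actually evaluable and restate its 1-β with the loss assumption shown.

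Cost: up to about 8 more patients per cohort (38 − 30), within the planned total, and somewhat longer accrual. For a cohort already closed, the cost is a less favourable stated 1-β.
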